### Secondary outcome measures

2.9

*Children's Yale-Brown Obsessive-Compulsive Scale*. OCD symptoms and OCD severity will be assessed with the Children's Yale-Brown Obsessive-Compulsive Scale (CY-BOCS) [31], a clinician rated semi-structured interview based on a combined parent and child-report and clinical evaluation. The CY-BOCS consists of a symptom checklist and a severity scale. The symptom checklist assesses current and past obsessive and compulsive experiences (indicated with ‘yes’ or ‘no’). The severity scale consists of 5 items on obsession severity and 5 items on compulsion severity, rated on a scale from 0 to 4. The total score is the sum of the obsessive and compulsive scale (0–40). A higher score indicates more severe OCD symptomatology. The CY-BOCS has good reliability (*α* = 0.87) and construct validity [38]. Comparable properties have been found for the Dutch translation of the CY-BOCS [39].

*Family Accommodation Scale-Anxiety.* The Family Accommodation Scale – Anxiety (FASA) [11] is a parent report measure and comprises 9 items rated on a Likert scale from 0 (never) to 4 (daily) that add up to the total accommodation score. Four additional items, rated from 0 (no) to 4 (extreme), assess the distress and consequences of family accommodation. The FASA-CR is a child-rated version with comparable items. The FASA (*α* = 0.87) and FASA-CR (*α* = 0.79) have shown good test-retest reliability in English speaking samples [40]. The validation of the Dutch version of the FASA and FASA-CR is currently in progress in a parallel study.

The *Coercive Disruptive Behavior Scale* – *Pediatric OCD* (CD-POC) [19,41] will measure coercive and disruptive behaviors of the child, that may lead to increased family accommodation [41]. Validation of the Dutch translation of the CD-POC is currently in progress. Emotional and behavioral problems of the child are assessed with the *Child Behavior Checklist* (CBCL, parent-report)*,* and its parallel versions: the *Teacher Report Form* (TRF; teacher-report) and the *Youth Self Report* (YSR, child-self-report, for children older than 11 years old) [42,43]. The *Screen for Childhood Anxiety Related Emotional Disorders-NL* (SCARED-NL, child-report) [44] is used to measure symptoms of anxiety. Symptoms of child depression are assessed by the *Children Depression Inventory-2* (CDI-2, child-report) [45,46]. Quality of life is measured using the *EuroQol 5D* (EQ-5D) for parents and *EuroQol 5D-Youth* (EQ-5D-Y) for children [47]. All instruments demonstrated sufficient to good psychometric qualities [19,42,45,[48], [49], [50]].

The *Clinical Global Impression-Severity and -Improvement scale* (CGI-S & CGI-I) [51,52] is used to measure change in psychopathological problems over time and filled in after every treatment session by the therapist. The CGI is found to be a reliable and valid instrument for routine use to measure clinical change [48]. The *Outcome Rating Scale* (ORS) and *Session Rating Scale* (SRS) [53,54] reported by parents is used to assess the treatment process. The ORS is filled in before the next session to report about past week and the SRS after every treatment session to report on the working alliance between parents and therapist. Higher scores indicate a higher well-being and treatment satisfaction. The ORS and SRS have shown good reliability and stable concurrent and construct validity [53,54] In addition, treatment satisfaction is evaluated directly after the end of the treatment (T4) with a 11-item questionnaire filled in by parents.

### Moderators and predictors of treatment outcome

2.10

Demographic variables such as gender, age of child, cultural background, family functioning, educational level, school functioning and life-events are assessed during intake and by an online standardized questionnaire. Psychiatric co-morbidities of the child will be assessed by the *Structured Clinical Interview for DSM-5 disorders* (SCID-5 junior) a reliable and valid instrument to assess DSM-5 diagnosis in children and adolescents [32]. Symptoms of autism reported by parents are assessed using the *Social Responsiveness Scale* (SRS-2) [55,56]. Reliability and criterium validity statistics are good [57].

Parental burden is measured with the Dutch *Parenting Stress Questionnaire* (Opvoedbelasting Vragenlijst; OBVL) [58], a self-report questionnaire that addresses five aspects: problems in the parent-child relationship, problems in parenting, depressed moods, role restriction, and health complaints. The Dutch Committee on Test and Testing rated the reliability of the OBVL as good and the constructed validity as sufficient [58]. The *Adult Self Report* (ASR) [59] is used to assess parental behavioral and emotional problems. The ARS is a reliable and valid instrument to measure adult psychopathology [60].

## Statistical analysis

3

### Plan of statistical analysis for the SCED primary study parameters

3.1

In this study, the main objective is to explore the efficacy of SPACE. The primary analysis focuses on the change in the frequent measure on OCD and FA between baseline phase (A) and treatment phase (B1+B2). First, individual participants data will be separately systematically visually analyzed [61]. Next, individual data will and modelled using a generalized least squares (GLS) approach (assuming autocorrelation) [62]. To test the treatment effect on group level, a multilevel modelling approach [63] based on the examples of Shadish and colleagues (2013) [64] and Moeyaert and colleagues [63,65,66] will be used. Data from all individual participants will be included in the multilevel model and structured across a hierarchical three-level structure. Level 1 represents the frequent measurement occasions, with measures being nested within each participant. Level 2 represents the individual participants (mothers, fathers and children), with family members being nested in a family unit. Level 3 represents the family units (e.g. members of one family) included in this study. Adding time-variant predictors (the number of measurement occasion to model general time trend, a dummy-coded variable (0–1) representing the phase and an interaction term between these two) at Level 1 allows to explore for a shift in level of OCD and FA at the start of the treatment phase and the shift in trend during the treatment phase [65]. Multiple plausible multilevel models will be estimated to enhance conclusions about the treatment effect [63]. For these analyses a significance level of 0.05 is used.

Exploratory, we expect the greatest shift in OCD severity and FA level in phase B2 when parents implement their plan to reduce FA. By starting phase B2 directly after implementation of the plan we aim to explore the immediate effect of the implementation and shift in OCD and FA level during the second half of the treatment. For this purpose, an additional time predictor at Level 1 will be added to estimate shift in level and shift in trend for phase B2.

For the secondary objectives, cross-level interactions will be added to the multilevel modelling approach to explore moderators effecting the efficacy of SPACE. To explore mechanisms of change, cross-lagged correlations will be calculated to explore the association between the frequent measure of OCD and FA over time (with respect to the direction of the association as well as the time-dependent association; [23,25]. Recent developments in the field of single-case mediation analysis (SCMA, [67]) will be used to explore mediation pathways.

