### Assessments

2.7

*Frequent assessments.* The frequent assessments obtain the primary outcome measures described as the ‘frequent measure on OCD and FA’, used for SCED analyses. During all phases (A-B1-B2-C), parents and children receive four short questions three times per week (on Mondays, Wednesdays, and Fridays) on OCD severity and FA. This will result in 72 frequent assessments for each participant (i.e. 72 assessments for each parent and 72 assessments for the child) over the total course of the study. It will result in approximately 12–24 frequent assessments during the baseline phase, 36 frequent assessments during the total treatment phase and again 12-24 frequent assessments during the follow-up phase. Participants are also asked to report any special events during the past week, each Friday during all phases. The measures are collected electronically using the smartphone application m-Path [36], designed to facilitate frequent assessments over time of participants feelings, thought, behaviors an experiences as they occur in daily life. This research methodology is often referred to as experience sampling method (ESM) [37].

*Standard clinical assessments*. The standard clinical assessments at timepoint T0-T5 and during every treatment session obtain the secondary outcomes measures, moderators and predictors of treatment response. An overview of all measures is listed in Table 2.

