### Primary outcome measure

2.8

*Frequent measure on OCD and FA.* The frequent measure is a brief 4-item questionnaire on the level and time spent on OCD and FA (see Table 3). The questions are developed in collaboration with experience experts from patient organizations and families who previously received therapy for their child's OCD. Each item is rated on a 11-point scale (0–10). Both parents and the child complete the questions independently of each other.

**Table 3 tbl3:** Frequent brief assessment questions on OCD and FA for parents and children.

	Question	Scale
OCD questions parents		
1	To what extent did your child experienced obsessions and compulsions today (including the night)?	0 (*not at all*) to 10 (*to the fullest extent*)
2	How much time did your child spend on obsessions and compulsions today (including the night)?	*0 min* to *more than 8 h*
FA questions parents		
3	To what extent did you accommodate to the obsessions and compulsions of your child today (including the night)?	0 (*not at all*) to 10 (*to the fullest extent*)
4	How much time did you spent accommodating to the obsessions and compulsions of your child today (including the night)?	*0 min* to *more than 8 h*
OCD questions child		
1	To what extent did you experienced obsessions and compulsions today (including the night)?	0 (*not at all*) to 10 (*to the fullest extent*)
2	How much time did you spend on obsessions and compulsions today (including the night)?	*0 min* to *more than 8 h*
FA questions child		
3	To what extent did your parents accommodate to your obsessions and compulsions today (including the night)?	0 (*not at all*) to 10 (*to the fullest extent*)
4	How much time did your parents spent accommodating to your obsessions and compulsions today (including the night)?	*0 min* to *more than 8 h*

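### The three-level group model has no family-by-occasion term although mother, father and child rate the same day, so its 5% tests can reject too often, most consistently for the trend shift

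*Protocol article*

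**What the plan says.** Section 3.1 describes one multilevel model holding the data of all participants. The lowest level is set out thus: "Level 1 represents the frequent measurement occasions, with measures being nested within each participant". The informants stand above it as units of their own: "Level 2 represents the individual participants (mothers, fathers and children), with family members being nested in a family unit". The family is the top of the hierarchy, and nothing else is placed there: "Level 3 represents the family units (e.g. members of one family) included in this study". Besides the occasion number, the model has as predictors "a dummy-coded variable (0–1) representing the phase and an interaction term between these two) at Level 1". They carry the shift in level and the shift in trend, tested at 0.05. The section does not say which coefficients are random or what residual covariance the group model uses. Autocorrelation is mentioned for the analysis of single series, which are "modelled using a generalized least squares (GLS) approach (assuming autocorrelation").

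Section 2.7 gives the schedule: "parents and children receive four short questions three times per week (on Mondays, Wednesdays, and Fridays) on OCD severity and FA". Table 3 in Section 2.8 gives the items. The parents' first OCD item reads "To what extent did your child experienced obsessions and compulsions today (including the night"), and the child answers the matching item about the same day. On FA, each parent rates their own accommodation and the child rates that of the parents.

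**The concern.** Within a family, occasion is crossed with informant: one Monday produces up to three ratings. The stated hierarchy treats occasions as nested in the informant. Informant and family effects remove what is constant over time for that person or family. A day that everyone in the family reports as bad is not constant over time, so it stays in the Level 1 residual of each informant. Conditional on the random effects, the model then counts two or three reports of one day as separate information on the phase and phase-by-time effects.

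At stake is the group-level efficacy statement. If the shared day matters, the standard errors of the level and trend shifts are too small and the stated 5% is not the real error rate.

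**Working it through.** **Inputs from the protocol article.** 25 families (Section 2.1). Up to three informants per family (Sections 2.8 and 3.1). Three prompts a week, so baselines of 4, 6 or 8 weeks give 12, 18 or 24 occasions and 12 treatment weeks give 36. Significance level 0.05, taken as two-sided because the side is not stated. Model terms: time, phase, phase by time.

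**Assumed.** The same-day residual correlation r between informants, 0.1 to 0.6; complete series from all informants; for the simulation, 24 families (8 per baseline length).

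**Closed form, random intercepts only.** Phase and time are identical for all informants of a family on a given date, so the shifts are estimated from family-day means. With m informants and residual variance s², the variance of such a mean is s²[1 + (m − 1)r]/m, while the model assumes s²/m. The standard error is too small by the factor √(1 + (m − 1)r), and the true error is 2[1 − Φ(1.96/√(1 + (m − 1)r))].

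| r | m = 3: factor | m = 3: true error | m = 2: factor | m = 2: true error |
|---|---|---|---|---|
| 0 | 1.00 | 5.0% | 1.00 | 5.0% |
| 0.1 | √1.2 = 1.10 | 7.4% | √1.1 = 1.05 | 6.2% |
| 0.3 | √1.6 = 1.26 | 12.1% | √1.3 = 1.14 | 8.6% |
| 0.5 | √2.0 = 1.41 | 16.6% | √1.5 = 1.22 | 11.0% |
| 0.6 | √2.2 = 1.48 | 18.6% | √1.6 = 1.26 | 12.1% |

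**Simulation with no treatment effect.** REML fit of the stated hierarchy, three informants, 500 runs per cell (Monte Carlo standard error about 1 point near 5%). Entries are rejection rates in %, level shift / trend shift, z test. The column r = 0 is the plan's own 5%, which is reproduced within simulation error when the random effects match the data.

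| Random coefficients fitted | Families and informants truly differ in response | r = 0 | r = 0.3 | r = 0.6 |
|---|---|---|---|---|
| Intercepts only | no | 6.2 / 3.2 | 11.6 / 11.2 | 20.6 / 17.8 |
| Intercepts and phase | no | 6.0 / 3.2 | 9.6 / 10.8 | 14.8 / 18.6 |
| All | no | 6.0 / 3.0 | 10.2 / 10.6 | 15.4 / 17.8 |
| Intercepts and phase | yes | 3.0 / 7.4 | 4.4 / 15.6 | 5.0 / 22.0 |
| All | yes | 5.4 / 3.8 | 6.4 / 9.4 | 7.0 / 15.0 |

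In the fourth row part of the trend error comes from leaving the trend fixed although it varies: it is 7.4% already at r = 0. A t reference with 23 degrees of freedom lowers the figures a little but does not remove the trend problem (last row: 8.0% and 13.0%). Residual autocorrelation of 0.3, when modelled, gives nearly the same results.

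**Same data, family-by-occasion random effect added** (400 runs per cell):

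| Random coefficients fitted | Families and informants truly differ in response | r = 0.3 | r = 0.6 |
|---|---|---|---|
| Intercepts only | no | 5.2 / 3.5 | 5.8 / 3.5 |
| All | no | 5.2 / 3.5 | 5.5 / 3.3 |
| All | yes | 7.0 / 3.5 | 6.0 / 3.7 |

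The trend test falls from 9.4–17.8% to 3.3–3.7%. The level test falls from 10.2–20.6% to 5.2–5.8% without true differences, and is unchanged within simulation error with them.

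**The case against.** The strongest reply is that the plan does not treat a family's ratings as independent. A reader who stops at the Level 1 sentence might infer that it does, but the next sentences nest informants in families. That stands: only the day-specific shared part is left out.

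Second, an article may leave random effects and residual covariance to an analysis plan, and Section 3.1 foresees several plausible multilevel models. This stands for the random effects, which is why the table runs over several choices. It does not answer the point. The article does state the levels, none of them is the family's day, and the sentence about several models names no such term.

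Third, r is unknown. At r = 0 there is no inflation, and at 0.1 it is slight. Missed prompts and one-parent families reduce the overlap further. For FA, mother and father rate different behaviour, although the child's rating concerns both. All of this stands and makes the conclusion conditional. Yet zero is hard to defend for OCD, where all informants describe one child's day; the plan itself collects special events every Friday.

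Fourth, the study is framed as exploring efficacy, and the individual analyses come first. Those use one series at a time and are unaffected. The group model is nevertheless the one said to test the treatment effect, at 0.05.

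**Conclusion.** The point holds conditionally. If the hierarchy is fitted as written and same-day residuals correlate at 0.1 to 0.6, the group-level 5% test has a true error of roughly 6% to 20%. The low end is two informants at r = 0.1; the high end is three informants at r = 0.6 with random intercepts only. The trend shift is affected in every setting tested. The level shift is close to nominal once all coefficients are random and families truly differ.

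Three stronger readings are not supported:
- That the primary test rejects too often as a matter of fact. This depends on a correlation the document does not give and on random effects it does not specify.
- That the group model ignores autocorrelation. Section 3.1 mentions autocorrelation for the individual models and is silent for the group model, so no figure is attached to this.
- That OCD and FA, or the exploratory moderator tests, suffer equally. FA is the weaker case, and the moderator tests were not checked.

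This should be fixed, but it does not invalidate the design.

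**What to change.** In Section 3.1, or in the analysis plan that implements it, state that the group models for OCD and FA include a family-by-occasion (family-date) random effect, or equivalently residuals that may correlate between informants of one family on one date. State that phase and trend effects are random at family level. Estimate the shared-day variance separately for OCD and FA, so that a smaller correlation for FA shows itself. As a sensitivity analysis, refit the model to family-day means; where an informant missed a prompt, account for who answered that day. Fix this before the outcome data are modelled, so that the choice cannot follow the results.

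The cost is one more variance term to estimate and somewhat wider intervals with less favourable p-values. No new data and no change to the conduct of the study are needed.

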### Randomization

2.4

Participants will be randomly allocated to a baseline length of four, six or eight weeks, to ensure internal validity [33]. Permuted block randomization will be used with blocks of 3 and 6 and be computerized (by the data collection system Castor EDC). It is not possible to blind the researcher conducting the assessments, since the following assessments (T1 – T5, see Fig. 1) depend on the baseline period that is randomly selected. All questionnaires will be completed online to reduce researcher influence.

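### With raw occasion number in the phase interaction, the phase coefficient is not the level shift at treatment start, and its error depends on the randomised baseline length

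*Protocol article*

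**What the plan says.** Section 3.1 (Plan of statistical analysis for the SCED primary study parameters) compares the frequent OCD and FA ratings in the baseline phase with those in the whole treatment phase. Visual analysis and individual GLS models come first. A three-level model then tests the effect at group level, with Level-1 predictors given as "the number of measurement occasion to model general time trend, a dummy-coded variable (0–1) representing the phase and an interaction term between these two". These are said to capture the "shift in level of OCD and FA at the start of the treatment phase and the shift in trend during the treatment phase".

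For the exploratory question about the start of plan implementation, "an additional time predictor at Level 1 will be added to estimate shift in level and shift in trend for phase B2".

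Section 2.4 staggers the start of treatment: "Participants will be randomly allocated to a baseline length of four, six or eight weeks". Section 2.7 expects "approximately 12–24 frequent assessments during the baseline phase, 36 frequent assessments during the total treatment phase".

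Section 3.1 mentions no centring of time at treatment start and no contrast evaluated there. It does not say which coefficients vary between participants or families, and it announces several plausible multilevel models.

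**The concern.** In a model with time, a phase dummy and their product, the dummy's coefficient is the phase difference where time equals zero. If time is the running occasion number, zero lies just before the first baseline prompt, weeks before treatment. The plan reads the terms as giving the shift at the start of treatment, which is a different quantity whenever the slope changes. A slope change is what the interaction is there to detect, and the plan itself expects the largest change partway through treatment.

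Because baselines are staggered, the extrapolation runs over a different distance in each randomised group. One pooled phase coefficient then mixes three quantities. One pooled interaction has to represent slope changes that begin at three different occasion numbers. At stake are the interpretation and power of the level-shift term in the group analysis of the primary outcome and, to a degree set by the random effects, the trend-change estimate.

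**Working it through.** **Inputs from the article.** Three prompts per week and baselines of 4, 6 or 8 weeks give 12, 18 or 24 baseline occasions. Treatment has 36 occasions and the follow-up remainder is 24, 18 or 12. Each row sums to the stated 72 (12 + 36 + 24, 18 + 36 + 18, 24 + 36 + 12). The first treatment occasion Ts is therefore about 13, 19 or 25. Outcomes are scored 0–10.

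**Assumed, because the article gives no effect sizes.** Level shift δ = −1 or 0; trend change γ = −0.05 or −0.02 per occasion (with one check at +0.03); flat baseline.

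**Algebra.** Write the fitted model as b0 + b1·T + b2·D + b3·D·T, with T the occasion number and D the phase dummy. Let the true effect be D·[δ + γ(T − Ts)]. Expanding, this is (δ − γ·Ts)·D + γ·D·T. So b2 = δ − γ·Ts and b3 = γ. This result does not depend on the assumed sizes.

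**Single-case values of b2.**

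| δ, γ | Ts = 13 | Ts = 19 | Ts = 25 |
|---|---|---|---|
| −1, −0.05 | −1 + 0.65 = −0.35 | −1 + 0.95 = −0.05 | −1 + 1.25 = +0.25 |
| 0, −0.05 | +0.65 | +0.95 | +1.25 |
| −1, −0.02 | −0.74 | −0.62 | −0.50 |
| −1, +0.03 | −1.39 | −1.57 | −1.75 |

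In every row b3 = γ exactly, and the shift can be recovered as b2 + b3·Ts. For example, −0.35 − 0.05 × 13 = −1.

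**Pooled model, δ = −1, γ = −0.05, noise-free, equal numbers per baseline length.** The random-effects rows are GLS limits with assumed residual SD 1.2 and random-intercept SD 1.

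| Coding and structure | Phase | Trend change | Attenuation of trend change |
|---|---|---|---|
| Raw, OLS | −0.38 | −0.0409 | 18% |
| Raw, family fixed intercepts | −0.21 | −0.0374 | 25% |
| Raw, random intercept | −0.22 | −0.0375 | 25% |
| Raw, plus random phase, SD 0.2 | −0.18 | −0.0403 | 19% |
| Raw, plus random phase, SD 0.35 | −0.14 | −0.0433 | 13% |
| Raw, plus random phase, SD 0.7 | −0.09 | −0.0472 | 6% |
| Raw, plus random phase, SD 1.0 | −0.07 | −0.0485 | 3% |
| Centred, OLS or family intercepts | −1.00 | −0.0500 | 0% |

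The OLS figure can be checked by hand. The variance of baseline length is 24. The within-phase variance of 36 consecutive occasions is (36² − 1)/12 = 107.9. The factor is 107.9/131.9 = 0.818, and 0.818 × −0.05 = −0.0409. The family-intercept fit also shows a spurious baseline trend of −0.0097 per occasion.

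**Later evaluation does not fully repair the pooled fit.** With family intercepts, b2 + b3·Ts is −0.2105 − 0.0374 × 13 = −0.70, then −0.2105 − 0.0374 × 19 = −0.92, then −0.2105 − 0.0374 × 25 = −1.15. The true value is −1 in all three groups.

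**Simulation.** The settings were 25 families with one series each, 180 replicates, AR(1) 0.2 and random-phase SD 0.2 or 0.7. Raw coding gave mean phase coefficients from −0.08 to −0.22, significant in 8–36% of runs. Centred coding gave −0.98 to −1.00, significant in 100%. Raw fits with a random phase effect gave trend changes of −0.045 to −0.048, about 4–10% too small. Centred fits gave −0.050 to −0.051.

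**B2.** A level shift and a trend shift are two parameters. One added predictor supplies one coefficient, so it cannot estimate both.

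**The case against.** The strongest reply is that section 3.1 never says where occasion numbering begins. If occasions were numbered from each participant's own treatment start, with baseline occasions negative, the same three predictors would give the intended shift. A cited methods paper or an unseen analysis plan may do this, and an article need not spell out such coding. It is true that the fuller documents may already be correct. But the article gives occasion number the role of general time trend, defines the interaction as the product of that variable with the dummy, and attaches an interpretation. Numbering from treatment start is not in the text, and an unseen source does not correct the model that is stated.

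Other parts of the reply stand:

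- **Trend bias.** A reader might infer that the trend-change estimate is biased throughout by about a quarter. The article does not support that. It leaves the random effects open and plans several models. The bias is absent in single-case fits and when the trend does not change, and it is mostly small with a random phase effect.
- **Sign.** A reader might infer that a gradual benefit always makes the level shift look like worsening. That is not general. With δ = −1 and γ = −0.05 only the 8-week group turns positive, the mean pooled coefficients stay negative, and with γ = −0.02 every group keeps its sign.
- **Role of the coefficient.** No single coefficient is named as the efficacy test, visual and individual analyses come first, and the predictors of the individual GLS models are not given.
- **B2.** This point rests on the literal wording of condensed prose about an exploratory analysis.
- **Missed prompts.** A reader might worry that skipped prompts compress the time scale. Nothing in the article says that missed prompts drop out of the numbering.

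**Conclusion.** The point holds for the level shift. As written, the phase coefficient is δ − γ·Ts and equals the shift at treatment start only if the trend does not change. Its error is γ multiplied by about 13, 19 or 25 according to randomised baseline. Under δ = −1 and γ = −0.05 the pooled coefficient is about −0.2 with family intercepts and common coefficients, so a real immediate drop of one point could easily be missed.

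For the trend change the point holds only in the pooled model, and its size cannot be settled from the article. Attenuation is about 18–25% with a common phase effect, about 3–10% in most fits with a random phase effect, and up to about 19% if that variance is small. The algebra is free of assumptions about effect size. Every numerical size given here rests on the assumed δ, γ and variance components.

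**What to change.** In section 3.1, define the interaction in the multilevel models as phase × (occasion − that participant's first treatment occasion), keeping occasion number as the general trend and the 0–1 phase dummy. The dummy then estimates the shift at treatment start and the interaction the change in trend. Use the same coding in the individual GLS models if they include these terms.

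For the exploratory B2 analysis, name two added terms: a B2 dummy, and B2 × (occasion − that participant's first B2 occasion).

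The cost is a change of wording and a few derived variables built from dates the study already records. No new data are needed. The coding should be fixed before the analysis begins.
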